#### Surgery

At the time of surgery, the following information will be assessed: date of surgery; type of procedure; duration of surgery; intraoperative complications according to the Clavien-Dindo-classification [18]; blood results at the time of or directly before the procedure, including C-reactive protein, lactate, leukocytes, glomerular filtration rate, creatinine, and hemoglobin; intraoperative hypotension; intraoperative blood loss; and aortic clamp time.

#### Sigmoidoscopy

At the time of sigmoidoscopy, the following information will be assessed and documented in a protocol: date of sigmoidoscopy; examination time; sigmoidoscopy findings (grade I: mucosal ischemia; grade II: mucosa and the muscularis layers; grade III: transmural ischemia, gangrene, and perforations; if grade III ischemia is detected, no biopsy will be performed); complications of the sigmoidoscopy; blood results, including C-reactive protein, lactate, leukocytes, glomerular filtration rate, creatinine, and hemoglobin; and a checklist to assess the degree of clinical suspicion of colonic ischemia filled out by the surgeon (if the checklist does not indicate a suspicion of colonic ischemia this will be defined as subclinical).

At the time of biopsy result, the following information will be assessed and documented in a protocol: date of result, biopsy findings differentiating ischemia in nongangrenous type (mucosal atrophy, edema, hyperemia, mild acute inflammation), and gangrenous type (acute wall necrosis), and ischemia grade.

Independent observers, blinded to the macroscopical findings of the sigmoidoscopy and the clinical course of the patient, will assess the results of the biopsy.

The tissue will be preserved for immunohistochemistry and RNA analysis of ischemia markers (eg, fatty acid binding protein).

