### End Points

The primary end point is the proportion of patients diagnosed endoscopically with subclinical and clinically relevant colonic ischemia among all patients undergoing aortic surgery.

The secondary end points are the proportion of patients requiring surgery for colonic ischemia after aortic surgery, the proportion of patients requiring stoma formation for colonic ischemia, perioperative in-hospital morbidity and mortality measured according to the Clavien-Dindo classification of surgical complications, length of hospital stay, and frequency of reoperation.

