### Number of Trial Participants

We assume that the rate of colonic ischemia diagnosed by sigmoidoscopy within 48 hours after the operation would be 10% in asymptomatic patients. In the current literature, the incidence of colonic ischemia diagnosed by clinical suspicion only in symptomatic patients is approximately 5%. This rate plus 10% of the 95% of asymptomatic patients results in an overall rate of patients with signs of colonic ischemia of 14.5%. In turn, this results in a 1-armed binomial distribution with 120 cases to be compared to the incidence reported in the literature (5%; α=5%; 1-β [power]=80%) [17].

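### The surgeon's suspicion checklist, which alone defines subclinical ischemia, is not required to be completed before the sigmoidoscopy result is known; the subclinical/clinical split can be biased, the primary proportion cannot

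*Protocol article*

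**What the plan says.** The Sigmoidoscopy part of Evaluation and Follow-up opens its list of data items with "At the time of sigmoidoscopy, the following information will be assessed and documented in a protocol". The list contains the endoscopic grade, complications of the examination, blood results and, last, "a checklist to assess the degree of clinical suspicion of colonic ischemia filled out by the surgeon". The decision rule follows in brackets: "if the checklist does not indicate a suspicion of colonic ischemia this will be defined as subclinical". No other criterion for the label is given.

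The same subsection states masking for a different assessment, the histology: "Independent observers, blinded to the macroscopical findings of the sigmoidoscopy and the clinical course of the patient, will assess the results of the biopsy". It says nothing about what the surgeon knows when completing the checklist.

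Nothing elsewhere places the checklist before the endoscopy. Table 1 puts data collection and ascertainment of the primary end point in the sigmoidoscopy column. The Results section ties the primary end point to the moment when the sigmoidoscopy and biopsy results are obtained.

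The label appears in two further places that matter here. End Points defines the primary end point as the "proportion of patients diagnosed endoscopically with subclinical and clinically relevant colonic ischemia among all patients undergoing aortic surgery". Number of Trial Participants assumes that "the rate of colonic ischemia diagnosed by sigmoidoscopy within 48 hours after the operation would be 10% in asymptomatic patients" and adds this to the symptomatic cases.

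**The concern.** The stated aim is the clinical value and safety of a planned sigmoidoscopy. Its diagnostic value over current practice lies in the ischemia it finds in patients whom nobody suspected, and the checklist separates those patients from the rest.

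Degree of suspicion is a judgement. If it is recorded once the endoscopic grade is known, a surgeon may report in good faith a suspicion that was not there beforehand. Subclinical cases then become clinical ones, and planned sigmoidoscopy appears to add less than it did. A judgement recorded with the result in hand cannot be reconstructed later, so analysis cannot repair this.

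The contrast with the biopsy reading makes the gap noticeable. Masking was considered and stated for the histology but not for the more subjective assessment.

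**Working it through.** **Which quantities depend on the label**

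| Quantity | Depends on the checklist? |
|---|---|
| Primary proportion and its 95% CI (End Points; Analysis of End Points) | No. Both labels are counted, so a relabelled case stays in the numerator |
| Comparison of the overall rate with 5% (Number of Trial Participants) | No. It uses the total |
| Rate in unsuspected patients, assumed 10% | Yes |
| Share of all ischemia that clinical suspicion detects | Yes |

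**Inputs**, all from Number of Trial Participants: N = 120; "the incidence of colonic ischemia diagnosed by clinical suspicion only in symptomatic patients is approximately 5" per cent; 10% among the remaining 95%.

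**The plan's own overall rate**

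5% + 10% × 95% = 5% + 9.5% = 14.5%, as stated.

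In 120 patients:
- clinical: 120 × 0.05 = 6.0
- subclinical: 120 × 0.95 × 0.10 = 11.4
- total: 17.4, and 17.4/120 = 14.5%

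**Effect of hindsight relabelling.** Let m be the share of subclinical cases marked as suspected because the result is known. The documents give no value for m, so a range is shown.

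- subclinical = 11.4 × (1 − m)
- clinical = 6.0 + 11.4 × m
- share apparently detected by suspicion = clinical / 17.4

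| m | Subclinical cases (% of 120) | Clinical cases (% of 120) | Total | Share apparently detected by suspicion |
|---|---|---|---|---|
| 0 | 11.40 (9.50%) | 6.00 (5.00%) | 14.5% | 34% |
| 0.1 | 10.26 (8.55%) | 7.14 (5.95%) | 14.5% | 41% |
| 0.2 | 9.12 (7.60%) | 8.28 (6.90%) | 14.5% | 48% |
| 0.3 | 7.98 (6.65%) | 9.42 (7.85%) | 14.5% | 54% |
| 0.5 | 5.70 (4.75%) | 11.70 (9.75%) | 14.5% | 67% |

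**Against the plan's 10% in asymptomatic patients.** The denominator is the unsuspected group, 120 × 0.95 = 114, and a relabelled patient leaves it. At m = 0.2 this gives 9.12 / (114 − 2.28) = 9.12 / 111.72 = 8.2%, against 11.4 / 114 = 10%.

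The calculation treats symptomatic in the sample-size section and suspected on the checklist as the same thing, which the article implies but does not say. It takes N = 120 as given and does not depend on how that number was derived.

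**The case against.** The strongest reply has three parts.

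*The main result is untouched.* This stands in full. A reader might infer that the primary end point is biased. The documents do not support that, because the end point sums the two categories and the total stays at 14.5% whatever m is. Nor is subclinical yield listed as an end point of its own or given its own analysis in Analysis of End Points. Its importance comes from the study aim and from the sample-size reasoning.

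*The article is silent, and silence is not exposure.* This stands in part. A reader might infer that the surgeon sees the result first. The text does not say so. It does not say who performs the endoscopy or whether the surgeon is present or informed, and the items are grouped by visit, so last place in the list is no evidence of order. Form-level detail is also often left to a fuller document. But the article does fix the assessor, the time and the decision rule for this checklist, and as fixed they allow the result to be known. It also found room to state masking for the biopsy readers.

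*The size is hypothetical and the bias might go either way.* The relabelled share is indeed an assumption. A reader might also infer that relabelling would inflate the subclinical yield just as readily. The documents give no support for that symmetry: only 6.0 clinical cases are expected, which limits movement in that direction, and nothing suggests that seeing ischemia would lead a surgeon to deny prior suspicion.

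**Conclusion.** The point holds in a limited form. As written, the protocol allows the checklist that alone defines subclinical ischemia to be completed with knowledge of the endoscopic result. This can bias the split between subclinical and clinically relevant ischemia, and with it the added yield of planned sigmoidoscopy. It cannot bias the primary proportion, its confidence interval or the comparison with 5%.

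With 20% relabelling, the subclinical rate loses 1.9 percentage points (9.5% to 7.6% of all patients), and clinical suspicion appears to detect about half of the ischemia instead of about a third. These figures rest on the plan's assumed rates, on equating symptomatic with suspected, and on a relabelling share that the documents do not give. They show how sensitive the split is and do not predict what will happen. The change is a cheap improvement; it does not correct an error in the main analysis.

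**What to change.** Add one sentence to Evaluation and Follow-up, Sigmoidoscopy: *The surgeon completes, dates, time-stamps and locks the suspicion checklist before the sigmoidoscopy starts.*

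The article gives June 2021 as the start of recruitment, so some patients may already have a checklist without a pre-endoscopy time stamp. Keep their data and report the subclinical/clinical split with and without them as a sensitivity analysis. Setting those checklists to missing would discard information for little gain. Keeping the checklist from the endoscopist is not needed to solve this problem.

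The cost is a time field on an existing form, some discipline on the ward and possibly an amendment notice, since the Discussion commits to submitting substantial changes to the ethics committee. The sample size, the primary end point and its analysis stay as they are.

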#### Discharge or Death of the Patient

In-hospital mortality and complications will be documented according to the Clavien-Dindo classification. For any operations performed due to a complication, details will be recorded (type of procedure, stoma formation etc).

### Ethics Approval

The study has been approved by the Ethical Committee of the Medical Faculty of the Martin-Luther University Halle-Wittenberg (application #2021-052).

## Results

The primary end point is the proportion of patients diagnosed endoscopically with subclinical and clinically relevant colonic ischemia among all patients undergoing aortic surgery. Patient recruitment started on June 2021. The final patient is expected to be treated by the end of June 2023. For each participant, the duration of the trial will be a treatment phase from recruitment into the trial until hospital discharge. The primary end point will be ascertained at the time of obtaining sigmoidoscopy and biopsy results. The total duration of the trial is expected to be 48 months.

## Discussion

This prospective study will provide insight into the clinical value and safety of performing routine sigmoidoscopy and biopsy for the detection of colonic ischemia in patients undergoing elective aortic surgery and further help determine whether the use of sigmoidoscopy in patients after an aortic surgery is safe. It will be conducted according to the presented protocol. The expected results will support health care professionals and patients with aortic aneurysms undergoing endovascular and open surgery in their decision-making concerning a planned sigmoidoscopy after the procedure. Specifically, we expect the results to provide sufficient data to develop risk scores for these patients. If this study shows that sigmoidoscopy can be performed safely and is effective in diagnosing colonic ischemia in these patients, it could be implemented routinely in both elective and emergency settings.

After due consideration, all participating investigators are convinced that the trial has a favorable risk-benefit ratio. The study has been approved by the Ethical Committee of the Medical Faculty of the Martin-Luther University Halle-Wittenberg. The innovative prospective design of this study in this context is also relevant for providing new knowledge in an international research context because, so far, only retrospective studies have been conducted on the given research topic. Colonic ischemia after aortic surgery is a relatively rare condition, with an incidence of approximately 5%. However, it bears severe clinical consequences with an in-hospital mortality of 26.7%-37.8% [9,10,13]. Colonoscopy and sigmoidoscopy have been proven to be sensitive and specific in diagnosing this pathology in the aortic surgery scenario [10-12] and are already a diagnostic standard when there is clinical suspicion [19]. Furthermore, based on the current data, no precise and evidence-based clinical, laboratory, or radiographic instruments that recognize colonic ischemia are available. Sigmoidoscopy has been described as a safe procedure with complication rates of 0.08%, with most complications being of mild severity [20]. However, these complication rates relate to a general population and not to patients after aortic surgery with possible colonic ischemia, in whom the risk for endoscopy-related complications is unclear and might be higher. Nonetheless, the additional risk posed to trial participants by sigmoidoscopy is estimated to be low according to the available cohort studies [20].

We state that according to the currently available evidence, the value of sigmoidoscopy and biopsy after endovascular and open surgery should be investigated to develop prediction scores that could identify patients at risk for colonic ischemia and facilitate their timely treatment. Patients with a delayed diagnosis of the condition have a high mortality. If a patient is diagnosed with subclinical ischemia, follow-up will be offered. All complications, both arising from sigmoidoscopy and the other aspects of the patients’ treatment, will be documented and reported to the principal investigator (AR). He can interrupt the trial at any point or, in accordance with the ethical committee, implement changes to the study protocol.

The study is being conducted in accordance with the applicable version of the declaration of Helsinki. Prior to study initiation, approval from the relevant ethical committee has been sought. Before enrolment into the trial, patients will be informed in writing and verbally about the nature and implications of the trial and especially about the possible benefits and risks to their health. Patients will document their consent by signing the informed consent form. Patients can leave the trial at any point without providing a reason for doing so. In such a case, treatment of the patient will continue according to the individual judgment of the treating physicians. Given that open aortic surgery and sigmoidoscopy are considered routine surgical and diagnostic treatments and given that the trial evaluates the value of sigmoidoscopy as a novel diagnostic sequence, there is no requirement for trial-specific patient insurance. Trial participants will be insured by the hospital’s insurance covering inpatient treatments. The trial has been registered in a publicly available repository (German Clinical Trials Register; DRKS00025587) for clinical trials prior to initiation. All planned substantial changes will be submitted for approval to the relevant ethical committees in writing as protocol amendments.

Concerning our dissemination plan, we aim to publish results from this trial in the form of one or several manuscripts in international medical journals. The principal investigator (AR) will review all manuscripts to prevent forfeiture of patent rights to data not in the public domain. The authorship list will be agreed on by the principal investigator prior to publication. Investigators from the participating departments will be offered authorship on manuscripts. Publication of the first manuscript reporting study results is planned to take place as soon as possible after analysis of the primary end point. Efforts will be made to ensure that the pertinent manuscript will not be submitted later than 6 months after the results are available.

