
The aim of this study is to evaluate the clinical value and safety of performing a planned sigmoidoscopy and biopsy for detection of colonic ischemia in patients undergoing elective aortic surgery. We also aim to develop prediction scores which could identify patients at risk for colonic ischemia and facilitate their timely treatment. If this study shows that sigmoidoscopy can be performed safely and is effective for diagnosing colonic ischemia in these patients, this could result in its routine implementation in both elective and emergency settings.

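### The protocol expects enough data to develop risk scores, but its own assumptions give about 17 events, enough for only about 1 to 4 model parameters

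*Protocol article*

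**What the plan says.** The Abstract (Objective) and the last paragraph of the Introduction give score development as an aim beside the evaluation of sigmoidoscopy: "We also aim to develop prediction scores which could identify patients at risk for colonic ischemia and facilitate their timely treatment". The Discussion then states what the trial should deliver: "we expect the results to provide sufficient data to develop risk scores for these patients".

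The section Number of Trial Participants is the only place where the size of the trial is justified. It starts from an assumption about patients without symptoms: "We assume that the rate of colonic ischemia diagnosed by sigmoidoscopy within 48 hours after the operation would be 10% in asymptomatic patients". It adds a literature rate of about 5% in symptomatic patients and reaches an "overall rate of patients with signs of colonic ischemia of 14.5" per cent. The size follows from a test of that rate: "1-armed binomial distribution with 120 cases to be compared to the incidence reported in the literature (5%; α=5%; 1-β [power]=80" per cent). The section does not mention prediction.

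Evaluation and Follow-up lists the information collected at trial entry, at surgery and at sigmoidoscopy. It names no subset intended for a score.

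**The concern.** How complex a prediction model can be depends mainly on the number of patients with the outcome, not on the number enrolled. A trial sized to separate 14.5% from 5% needs few events. A multivariable score needs many more, because each parameter is estimated from the same small group of cases. The sample-size section settles the first question, and the Discussion claims the second without a supporting argument.

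The scores are meant to identify patients at risk and bring treatment forward. A score with more parameters than the data support would discriminate well in the patients it was fitted to and less well in new ones. A reader who trusted the statement of sufficiency would have no warning of this.

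**Working it through.** **Inputs.** From Number of Trial Participants: N = 120, 5% symptomatic, 10% of the remaining 95%. Assumed, because the article gives no figure: target shrinkage S = 0.9 (a conventional choice) and Nagelkerke R² of 15%, 30% or 50%.

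**1. The plan's own rate.** 0.05 + 0.95 × 0.10 = 0.145. This reproduces.

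The size of 120 does not reproduce as a one-arm test. Exact binomial calculation gives 62 to 69 patients at one-sided 5%, or 69 to 77 at one-sided 2.5%. That is a separate matter; 120 is the planned number and is used as it stands.

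**2. Expected events.**
- Total: 120 × 0.145 = 17.4; 95% binomial range 10 to 25.
- Symptomatic: 120 × 0.05 = 6.0.
- Subclinical: 120 × 0.95 × 0.10 = 11.4.

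These counts assume that all 120 patients have an evaluable sigmoidoscopy.

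**3. Largest possible R² at this event rate.**
- Null log-likelihood per patient: 0.145 × ln 0.145 + 0.855 × ln 0.855 = −0.414.
- Maximum Cox-Snell R² = 1 − exp(2 × −0.414) = 0.563.

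**4. Parameters that 120 patients support.** The shrinkage criterion is n = P / [(S − 1) × ln(1 − R²cs/S)], with R²cs = Nagelkerke R² × 0.563. Solved for P at n = 120:

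| Assumed Nagelkerke R² | R²cs | Patients per parameter | Parameters at n = 120 |
|---|---|---|---|
| 15% | 0.0845 | about 101 | 1.2 |
| 30% | 0.169 | about 48 | 2.5 |
| 50% | 0.282 | about 27 | 4.5 |

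In whole parameters this is about 1 to 4. A simpler rule of 5 to 10 events per parameter (also an assumption) gives 17.4/10 = 1.7 to 17.4/5 = 3.5, which agrees.

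**5. Sensitivity to the event rate.** The Introduction cites 20.8% with colonic ischemia at routine endoscopy, in a mixed elective and emergency population. That rate gives 120 × 0.208 = 25.0 events. The maximum Cox-Snell R² becomes 0.640, and the same formula gives 1.4 parameters (R² 15%) to 5.3 (R² 50%). The conclusion does not change.

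**6. Illustration of optimism.** Data were simulated with n = 120, a 14.5% event rate and predictors unrelated to the outcome, and fitted by ordinary logistic regression without correction. The mean apparent AUC was 0.59 with 2 predictors, 0.66 with 5 and 0.73 with 10; the true value is 0.50. This shows how quickly apparent performance inflates at this size. It does not forecast what the trial will report, because the article does not state a fitting method.

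**The case against.** The strongest reply is that the article proposes no particular model. It gives no number of predictors, selection method or validation step, and these are commonly left to a full protocol or analysis plan that is not shown. The sentence is an expectation in the Discussion, and score development is neither a primary nor a secondary end point. Developing a score is not the same as using it. A small model is possible with these data, so it would be wrong to say that nothing can be done.

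Much of this stands, and it limits the point. Counting everything under Evaluation and Follow-up except dates and the suspicion checklist gives 14 items at entry, 12 at surgery and 6 blood results at sigmoidoscopy, 32 in all. A reader might infer that the trial has 17.4/32, about 0.5, events per predictor. The document does not support that reading:
- It never calls these variables predictors or says that all enter a model.
- Some overlap, such as creatinine and glomerular filtration rate.
- The blood results taken at sigmoidoscopy come too late for a score that would select patients for it.

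A reader might also infer that the trial will issue an overfitted score that misleads care. The article does not say that a score from this trial would be used without further validation. Its conditional remark about routine implementation concerns sigmoidoscopy.

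What does not stand is the appeal to an unseen plan. Such a plan can choose predictors, penalise and correct for optimism, but it cannot add events. The article makes a positive statement about sufficiency, and its own figures bound what that can mean.

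**Conclusion.** The point holds in a limited form. The expectation of sufficient data for risk scores has no support in the sample-size section. On the protocol's own assumptions there are about 17 events (range 10 to 25), of which about 6 are symptomatic, and these support about 1 to 4 parameters. The event count follows from the document. The parameter count rests on the shrinkage target of 0.9 and the assumed R² range of 15% to 50%, and the 5-to-10 events rule gives a similar answer. The data could suffice for a very small exploratory model, and the article does not state that limit. The primary end point and its confidence interval are not affected.

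**What to change.** Replace the sufficiency statement in the Discussion, and the matching aim in the Abstract and Introduction, with an exploratory aim. It should say that about 17 events are expected, that they allow only a very small model, and that any score needs external validation before use.

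For the analysis:
- Fix one or two predictors in advance that are available before sigmoidoscopy, for example open versus endovascular repair and patency of the inferior mesenteric artery.
- Fit a penalised logistic model. Ridge is suitable. Firth needs an intercept correction, because without it predicted risks at a 14.5% event rate are biased upward.
- Report bootstrap optimism-corrected discrimination and calibration.
- Present other associations descriptively.

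The cost is a less favourable stated aim and a little more analysis work. No new data or patients are needed.
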